The WORC is used in research [17] and has already been translated into German [18], Iranian [19], Norwegian [20], Portuguese [21] and Turkish [22]. A Dutch translation of the WORC will be used in our clinic. This translation was performed by linguistic validation, which is not a literal translation but a stepwise process to produce a conceptually equivalent of the original questionnaire[23]. The process was controlled with final approval by one of the authors of WORC[15]. In this study the Dutch version of the WORC is validated.

As far as we know the WORC has not been tested on a group of patients with arthroscopic rotator cuff repair. In the WORC article by Kirkley et al[15]. validity as an evaluative tool was tested in a group of 50 patients with disorders of the rotator cuff (DRC) who reported that their symptoms had changed. Forty-six were treated with injection therapy and only four underwent subacromial decompression[15]. In order to use the test in those who underwent arthroscopic rotator cuff repair, the WORC should be tested in a group of patients treated with this type of repair.

The aim of this study is to investigate reliability, validity and responsiveness of WORC in patients undergoing arthroscopic rotator cuff repair. Because there is no gold standard we are aiming to assess construct validity, i.e. the extent to which WORC scores relate to SF-36 and Constant Scores. More experiences with the disease specificity of the use of the WORC are needed, since this instrument is designed for use in patients with DRC only.

Therefore, three groups of patients are chosen in which the WORC will be tested. These groups contain patients with respectively:

1. Arthroscopic rotator cuff repair;

2. DRC without rupture;

3. Shoulder instability.

We hypothesize that the Dutch translation of WORC:

• has a high reliability (ICC > 0,9) in all 3 groups;

• has a high validity compared to SF-36 and Constant Scores in groups 1 and 2. We expect correlations on the SF-36 and Constant Score to lie around 0.6 and an inverse correlation between Constant Score and SF-36 versus WORC around -0.5[22]; The relation is expected to be negative due to the construction of WORC, in which a high score corresponds to a disabled shoulder, while a high Constant Score and SF-36 match with little disability.

• has a high responsiveness in groups 1 and 2;

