## Methods/Design

### Patient assignment

The WORC, as a disease-specific evaluation instrument, was developed for patients with a DRC[15]. In order to investigate reliability, validity and responsiveness of the WORC in patients with arthroscopic rotator cuff repair, data from patients undergoing an arthroscopic rotator cuff repair are analysed (group 1). To investigate disease-specificity of the WORC when compared to a different DRC, a second group 'non-Ruptured DRC' is added (group 2). This group includes the rest of rotator cuff pathology like rotator cuff tendonitis and tendinosis[15]. Bursitis and calcifying tendonitis are also included in non-Ruptured DRC. A third group consisting of patients with 'Shoulder Instability' is included in order to investigate the disease-specificity of WORC when compared to a different shoulder disease (group 3). Each group will consist of 30 patients in which we assume that at least one group will differ 25% on WORC score from the other groups, which yields an 80% power with a one sided α of 5%. This would also provide ample power for test-retest reliability with correlation coefficient of at least 0.95[28].

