### Reliability

Reliability of the WORC is tested by comparing the results at T0 with T1. T1 is planned 2-3 weeks after T0, because we expect that the symptoms do not change between these two moments and the time span is large enough to forget initial responses to the questions. In order to signal change in severity of the symptoms, at both moments patients are asked to rate their shoulder hindrance. To determine test-retest reliability, intraclass correlation coefficients (ICC) are used.

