By now, arthroscopic rotator cuff repair is a commonly accepted treatment. We also want to use the WORC to measure the results of our arthroscopic rotator cuff repairs. In patients with DRC the WORC is an appropriate measurement tool[15]. We will investigate whether this also accounts in patients with arthroscopic rotator cuff repair. To do so we investigate a group of patients with arthroscopic rotator cuff repair. A second group is used existing of patients with DRC analogical to the group used by the developers of the WORC. And in order to investigate specificity within the shoulder pathologies it is tested on a group of patients with a different type of shoulder complain, instability.

Reliability is tested by comparing T1 and T0 in the three groups. Concerning validity we are aiming to assess construct validity, i.e. the extent to which WORC Scores relate to SF-36 and Constant Scores. Construct validity can be assessed by comparing the convergent/discriminant validity across instruments and patient groups ('known-groups validation', hence the three patient groups). It should be noted that the study will not truly be able to assess disease specificity of the WORC because the three patient groups differ not only with respect to diagnosis, but also with respect to treatment modality. The Constant Score was elected to correlate with, because it is a clinical score which is commonly used and widely accepted in Europe[13]. Responsiveness is tested by comparing T2 and T0.

The name of the WORC implies specificity to rotator cuff disease, although it has been developed to assess quality of life regarding DRC, and not as a discriminative tool[15]. Therefore, the results of the WORC in group 1 and 2 are compared with a third group consisting of patients with instability to investigate specificity.

The method of patient assignment could be a subject of criticism. Patients were assigned to a certain group based on a combination of clinical symptoms and findings on MRI, Ultrasound or X-ray, because the clinical tests for DRC and shoulder instability lack high accuracy[30,54-58]. However, this was then confirmed during arthroscopy.

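### The power called ample for test-retest reliability does not hold for the protocol's own hypothesis: 30 per group gives about 61% power per group, and 23% for all three, at a true ICC of 0.95 against 0.90

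*Protocol article*

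**What the plan says.** - **Hypothesis (Background).** The Dutch WORC "has a high reliability (ICC > 0,9) in all 3 groups".
- **Sample size (Patient assignment).** "Each group will consist of 30 patients". This is justified by the comparison of WORC scores between groups, at 80% power and a one-sided alpha of 5%.
- **Reliability power (Patient assignment).** The next sentence extends the justification: "This would also provide ample power for test-retest reliability with correlation coefficient of at least 0.95". It cites a reference, but gives no null value, no alpha and no power percentage for reliability.
- **Method (Reliability).** "Reliability of the WORC is tested by comparing the results at T0 with T1", that is, two measurements per patient. "To determine test-retest reliability, intraclass correlation coefficients (ICC) are used".
- **Unit of analysis (Discussion).** "Reliability is tested by comparing T1 and T0 in the three groups".

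**The concern.** The article commits to a high bar, an ICC above 0.9 in each of three groups. It tells the reader that 30 per group is comfortably enough if the true coefficient is at least 0.95. The gap from 0.90 to 0.95 is narrow for 30 patients measured twice, so the assurance needs checking against the bar that the article itself sets.

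Reliability is the first property named in the aim. A reader who relies on the assurance could go wrong in two ways. If formal tests or confidence bounds decide, a group that misses 0.9 could be taken as evidence of poorer reliability when the sample was too small to show it. If point estimates decide, the hypothesis could be reported as confirmed for a group whose true ICC is at or below 0.9.

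**Working it through.** **Inputs**
- n = 30 per group; three groups (Patient assignment; Discussion).
- k = 2 occasions, T0 and T1 (Reliability).
- True ICC 0.95, the lower end of the stated range (Patient assignment).
- Null ICC 0.90. *Assumption:* the article states no null for reliability; 0.9 in Background is its only threshold.
- Alpha one-sided 5%. *Assumption:* stated for the group comparison and carried over.

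The plan gives no reliability power figure, so there is none to reproduce.

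**Formula.** For k = 2 in a one-way model, the ratio of between-patient to within-patient expected mean squares is θ = (1 + ICC)/(1 − ICC).
- ICC 0.90: θ = 1.90/0.10 = 19
- ICC 0.95: θ = 1.95/0.05 = 39

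The observed mean-square ratio divided by the true θ follows F with 29 and 30 degrees of freedom, so

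power = P(F[29,30] > Fcrit × θ0/θ1).

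**Power at a true ICC of 0.95 against 0.90**
- One-sided 5%: Fcrit = 1.847; 1.847 × 19/39 = 0.900; power = **0.611**.
- All three groups, independent, 0.95 in each: 0.611³ = **0.228**.
- One-sided 2.5% (lower limit of the two-sided 95% CI above 0.9): Fcrit = 2.083; 2.083 × 19/39 = 1.015; power = **0.484**; cubed, 0.113.
- Cross-checks at one-sided 5%: 0.603 with two-way degrees of freedom (29, 29), 0.615 with the Walter-Eliasziw-Donner approximation, 0.588 to 0.608 with Fisher's z.

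**Higher true ICC, null 0.90, one-sided 5%**

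| True ICC | θ1 | Power per group | All three |
|---|---|---|---|
| 0.95 | 39 | 61% | 23% |
| 0.96 | 49 | 81% | 54% |
| 0.97 | 65.7 | 95% | 86% |

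**Lower null, true ICC 0.95, one-sided 5%**

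| Null ICC | θ0 | Power per group |
|---|---|---|
| 0.88 | 15.7 | 79% |
| 0.85 | 12.3 | 92% |
| 0.80 | 9 | 99% |

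**If a point estimate above 0.9 were the criterion.** P(estimate > 0.9) = P(F[29,30] > 19/θ1):
- true ICC 0.95: 19/39 = 0.487, probability 97% (all three: 92%);
- true ICC 0.90: 19/19 = 1, probability 50%;
- true ICC 0.88: 19/15.7 = 1.213, probability 30%.

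**Precision.** At an observed ICC of 0.95 the mean-square ratio is 39. The two-sided 95% limits for θ are 39/2.083 = 18.73 and 39 × 2.092 = 81.60. Converted back by (θ − 1)/(θ + 1), the interval is 0.899 to 0.976, so it just includes 0.9.

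**Size needed at a true ICC of 0.95 against 0.90, one-sided 5%.** About 50 per group for 80% power in one group (exact F: 79.9% at 49, 80.6% at 50), and about 77 per group for 80% in all three jointly.

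**The case against.** The strongest reply is that the null is supplied here and not by the article. The reliability sentence names none, the cited reference is not at hand, and the Reliability section says only that ICCs are used. ICC above 0.9 appears in a list of hypotheses that also contains loosely worded expectations. Against a null of 0.85 or 0.80 the power at 0.95 is 92% or 99%, and ample would be a fair word. This stands. A reader might infer that the statement is an arithmetic error, or that it is true only against a trivial null such as zero correlation. The article does not support either reading.

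It is also fair that the stated range is open upwards. At a true ICC of 0.97, power is good both per group and jointly. But an assurance given for at least 0.95 has to hold at 0.95.

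A third reply is that no formal test may be meant. On a point-estimate reading, an instrument with a true ICC of 0.95 would clear 0.9 in a given group about 97% of the time. A reader should therefore not infer that such an instrument will probably fail in any one group; even under the formal test it succeeds there about 61% of the time. But the point-estimate rule also passes half the time at exactly 0.90 and 30% of the time at 0.88. It is no test of the hypothesis, and the word power presupposes a test.

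Finally, the study was sized on the group comparison and reliability is an added remark; an interval of about 0.90 to 0.98 is informative. That limits the severity but does not make the remark correct for the hypothesis.

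**Conclusion.** The point holds in this form: the power is not ample for the protocol's own hypothesis of ICC above 0.9 in all three groups. At the lower end of the range that the article names, power is about 61% per group (48% at one-sided 2.5%) and about 23% for all three. None of the methods tried reaches 80%, the level that the article uses for its group comparison.

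This rests on 0.90 as the null, a one-sided 5% alpha carried over from the group comparison, 30 analysable patients per group with two measurements each and, for the joint figure, independent groups with a true ICC of 0.95 in each. Under a lower null or a higher true ICC the statement could be true, but the article gives no lower null, and its hypothesis sets 0.9. Severity: should be fixed. It does not show that the study is unsound or needs more patients.

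**What to change.** 1. Replace the reliability power statement under Patient assignment. Either give the power with its assumptions (about 61% per group and 23% for all three, true ICC 0.95 against 0.90, one-sided 5%), or give the expected precision (95% CI about 0.90 to 0.98 at an observed ICC of 0.95 with 30 patients).
2. Report each group's ICC with its 95% CI, and claim ICC above 0.9 for a group only when the lower confidence bound exceeds 0.9. Say which bound is meant: 61% and 23% belong to a one-sided 95% bound; with the lower limit of the two-sided 95% CI they become 48% and 11%.
3. A within-group ICC pooled over all 90 patients may be added as a supplementary summary; its power against 0.90 at 0.95 is about 95%. It must not replace the per-group hypothesis, because it can hide a failing group. For example, with assumed true ICCs of 0.97, 0.97 and 0.88 and equal total variance, the pooled value is about (0.97 + 0.97 + 0.88)/3 = 0.94.

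The cost is a change of text and confidence intervals in the report, with no extra patients. The downside is that the stated power looks less favourable.

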#### Signs and symptoms

Group-1: Patients undergoing arthroscopic rotator cuff repair. These patients have a clinical suspicion of a symptomatic rotator cuff tear and a partial or full thickness lesion seen on MRI or Ultrasound and confirmed during the arthroscopic repair procedure. A clinical suspicion will be considered present in case of two or more of the following signs: Impingement (Neer's impingement sign or Hawkins-Kennedy impingement sign), Painful arc sign, positive Jobe test (supraspinatus), positive infraspinatus test (resistance test with external rotation at the side and in 90 degrees of abduction), positive lift-off/belly press test (resistance test of subscapularis) [29], positive Drop-arm test [30], positive Neer impingement test [29] (subacromial injection with lidocaine).

Group-2: Patients diagnosed as having non-Ruptured DRC. They have a clinical suspicion of DRC and no rupture of the rotator cuff on MRI or Ultrasound. A clinical suspicion will be considered present in case of two or more of the following signs: Impingement (Neer's impingement sign or Hawkins-Kennedy impingement sign), Painful arc sign, positive Jobe test (supraspinatus), positive infraspinatus test (resistance test with external rotation at the side and in 90 degrees of abduction), positive lift-off/belly press test (resistance test of subscapularis) [29] and positive Neer impingement test (subacromial injection with lidocaine). Patients are also assigned to Group-2 if the symptoms are accompanied by calcification of the tendon close to the greater tuberosity seen on X-ray. In that case further imaging like MRI or Ultrasound is not performed necessarily.

Group-3: Patients diagnosed with shoulder instability. They fulfil at least three of the following criteria: history of gleno-humeral dislocation, history of sense of instability, positive apprehension test, positive relocation test, glenohumeral translation, positive sulcus sign [29], positive jerktest [31], positive hyperabduction test [32], labral lesion on MRI, capsular lesion or laxity on MRI.

For a clear description of the clinical tests we refer to the appendix section.

#### Patient routine

Prior to the first visit to the orthopaedic shoulder outpatient clinic, consecutively, all new patients above age 18 are informed about the study by telephone. Patients who have difficulty understanding the explanation, because of language deficiency are excluded. The patient routine contains three measurement moments T0, T1 and T2.

During the first visit (T0), all new patients are asked whether they want to participate in the research project. If the answer is positive, the patients sign an informed consent form. Then a thorough history is taken and the patients will undergo a physical examination including the above mentioned clinical tests by the second author ([name]). Subsequently, scores on the WORC, SF-36 and the Constant Score are obtained, and patients are asked to rate their shoulder hindrance on an 11-point scale from 0 (no hindrance) to 10 points (extreme hindrance), all by the second author ([name]). (See the appendix section for details on obtaining the Constant Score.) In case of suspicion of instability or a cuff tear MRI is performed. If MRI is contraindicated and a cuff tear is suspected ultrasound is performed. Patients do not receive any therapy at T0.

The next visit is scheduled 2-3 weeks after T0. This visit is defined as T1. At T1 the WORC, SF-36 and Constant Score are scored again. In addition, the patients are asked to rate their shoulder hindrance on the 11-point scale to check whether their symptoms have changed since their last visit.

At T1 either conservative treatment is started or the indication for surgery is made.

In Group 1 an arthroscopic rotator cuff repair is performed. In case of an irreparable cuff tear due to size, atrophy or fatty degeneration the patient is excluded from the study.

In Group 2 conservative treatment is started by injection, physiotherapy and activity adjustment. Surgery is performed when conservative treatment failed. Arthroscopic subacromial decompression is in those cases performed and in patients with calcific tendonitis the calcium deposit is removed. If during arthroscopy an asymptomatic cuff tear is found it is repaired, but these patients are then excluded from the study.

In Group 3 patients receive conservative treatment or surgery when indicated. A labral or capsular repair is performed as needed.

Patients eligible for assignment to more than one group (e.g., those with both instability and impingement) are excluded from our study, because specificity of the WORC between the groups cannot be measured.

Patients with additional shoulder pathology like adhesive capsulitis, AC-pathology and osteoarthritis are excluded and patients with previous surgery are excluded as well.

At T2, either six weeks after starting conservative therapy or three months after operative therapy, the WORC, SF-36 and Constant Score are obtained again.

Patient characteristics like age, sex, hand dominance and Workers' Compensation claim are recorded and taken into account during data analyses, because we are comparing groups. If power permits we will control these group-characteristics.

Data will be analyzed with SPSS 15. Retrieved data from T0 and T1 will be checked for completeness and entered into Excel.

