The UCLA Shoulder Rating Scale is a combination of physical examination and subjective evaluation of complaints of patients by the attending physician. No publications are available with respect to the development and validation of this instrument. Therefore it is unknown why the developers of this instrument assigned the various weights to the 5 domains. While not necessarily incorrect, it is thus far unsupported[13]. The Constant Score also consists of a combination of physical examination and subjective evaluation filled out by the attending physician. The publication by Constant et al[14]. does not describe the methodology according to which the instrument was developed and more specifically, the rationale for item selection and relative weighing of the items[13].

Both scores are filled out by the attending physician. Kirkley et al. stated that it had been shown that physicians tend to evaluate their patients functioning better than the patients perceive it themselves, making it important for measurement tools to be self-administered[15].

Validated outcome measures need to be used in randomized controlled trials of interventions for rotator cuff tears. In such trials, disease specific quality of life questionnaires could be a core outcome domain [16] in addition to pain, shoulder specific function, and work ability. Most therapies in orthopaedic medicine are designed to improve quality of life rather than to prolong a patient's life. Therefore, it is important to assess quality of life when such therapies are evaluated. Arthroscopic rotator cuff repair is also performed to improve quality of life, which depends on shoulder functioning relevant for day-to-day activities. Hence, health-related quality of life patient-administered questionnaires (HRQL-questionnaires) are needed[15]. The Western Ontario Rotator Cuff Index (WORC) is a disease-specific quality of life questionnaire (QoL-questionnaire) designed for patients with disorders of the rotator cuff (DRC), which was published in 2003 [15] with a clear description on how the items were chosen, formulated and weighted. For further details of WORC we refer to the appendix section.

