### Responsiveness

Responsiveness, or the ability of an instrument to detect clinically important change, will be determined by calculating the standardized response means and effect sizes on T0 and T2 scores on WORC, SF-36 and Constant scores for the subgroups. The magnitude of the standardized response mean (mean change in score from T0 to follow-up (T2)/standard deviation of change in score) and the effect sizes (mean change in score from T0 to follow-up (T2)/standard deviation of T0 score) will be interpreted using the Cohen standard of greater than 0.20 for small effects, greater than 0.50 for moderate effects, and greater than 0.80 for large effects.

Finally, a comparison of WORC scores between the three distinct groups is made, to see whether WORC scores can differentiate between them. WORC scores will be compared with SF-36 to investigate whether the noted differences correlate with notable clinical differences and can be expressed as MCID's (minimal clinical important differences)[33].

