### Clinical tests

#### Impingement

Impingement is considered positive if the Neer's impingement sign or Hawkins-Kennedy impingement sign is present. Neer's impingement sign is positive if a forcible elevation of the arm with the scapula stabilized causes the pain[29].

The Hawkins-Kennedy impingement sign involves forward flexing the humerus to 90° and forcibly internally rotating the shoulder. This manoeuvre drives the greater tuberosity under the coracoacromial ligament similarly reproducing the impingement pain[29].

The Neer impingement test documents the patient's response to an injection of lidocaine into the subacromial bursa. An attempt to elicit the impingement sign is repeated. A significant reduction or abolition of the patient's pain constitutes a positive result of the impingement test[29].

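### At T0 all scores follow an examination that can itself change shoulder pain, and no matching conditions are fixed for T1 and T2, so comparisons that use T0 can be distorted

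*Protocol article*

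**What the plan says.** The article's Patient routine section sets the sequence at T0. After consent, "Then a thorough history is taken and the patients will undergo a physical examination including the above mentioned clinical tests". The next step is scoring: "Subsequently, scores on the WORC, SF-36 and the Constant Score are obtained, and patients are asked to rate their shoulder hindrance". The scale runs "from 0 (no hindrance) to 10 points (extreme hindrance), all by the second author", the person who also does the examination.

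The tests meant are those under Signs and symptoms. For groups 1 and 2 they include impingement signs, resistance tests and a "positive Neer impingement test (subacromial injection with lidocaine". The appendix (Impingement) says of that injection test: "A significant reduction or abolition of the patient's pain constitutes a positive result of the impingement test". The same section describes Neer's sign as positive when forced elevation of the arm brings on the pain.

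For T1, two to three weeks later, Patient routine says only that the three instruments are scored again and hindrance is re-rated. For T2 it says that the three instruments are obtained again. Neither visit has an examination, an order or an assessor described.

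T0 is used in four places. Reliability compares WORC at T0 and T1 by ICC. Validity uses T0 and T1. Responsiveness rests on the "mean change in score from T0 to follow-up (T2"), with the T0 standard deviation as the effect-size denominator. The hindrance ratings at T0 and T1 are the check that symptoms stayed stable. The Background sets the reliability target at an ICC above 0.9 in all three groups.

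**The concern.** On the article's own definitions, some of the tests done just before scoring at T0 provoke pain and one can abolish it. Scores taken straight afterwards may reflect the examination as well as the patient's usual state. The exposure is most direct for the Constant Score, whose components include pain, range of movement and strength (appendix, Constant Score). For the WORC and SF-36 it is less direct.

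If T1 and T2 are scored under other conditions, a disturbance confined to T0 would look like measurement error in the WORC test-retest comparison and would move every T0-T2 change. It would also enter the T0 validity correlations. The planned safeguard cannot separate this from real change, because the T0 hindrance rating follows the same tests. It could signal a change that did not occur or hide one that did. No later analysis can recover an undisturbed T0 score.

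**Working it through.** The article gives no figure for carry-over from the examination, so there is none to reproduce. Its sample size of 30 per group does not enter this point. What follows is an illustration.

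**Inputs**
- Undisturbed ICC 0.95: assumed here. It equals the coefficient that the sample-size sentence uses.
- SD 20 on a 0-100 scale: assumed, since the article states no SD.
- Half the patients shifted by s points at T0 and none at T1: assumed.
- Target, ICC above 0.9: from the Background.

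**Model.** Total variance is 20² = 400. Between-patient variance is B = 0.95 × 400 = 380, and error variance is E = 20. Shifting half the patients by s at T0 only gives:
- mean shift d = s/2;
- extra T0 variance v = s² × 0.5 × 0.5 = s²/4.

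Then:
- consistency ICC = B / (B + E + v/2);
- agreement ICC = B / (B + E + v/2 + d²/2).

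**Results**

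| s | d | v | Consistency | Agreement |
|---|---|---|---|---|
| 5 | 2.5 | 6.25 | 380/403.125 = 0.943 | 380/406.25 = 0.935 |
| 10 | 5 | 25 | 380/412.5 = 0.921 | 380/425 = 0.894 |
| 15 | 7.5 | 56.25 | 380/428.125 = 0.888 | 380/456.25 = 0.833 |

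At 5 points both forms meet the target. At 10 points only the agreement form misses it, by 0.006. At 15 points both miss. The sign of the shift does not matter for the ICC.

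**If every patient shifts equally.** Then v = 0 and the consistency ICC stays at 0.95. In SD units the agreement ICC is 0.95 / (1 + d²/2), which reaches 0.90 when d = √(2 × (0.95/0.90 − 1)) = 0.33 SD. Partial exposure, as when only some patients are injected, is what lowers the consistency form.

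**Responsiveness.** With the T0 SD held fixed, a mean T0 shift of d SD changes the effect size by d. A shift of 0.2 SD turns an effect size of 0.80 into 0.60 or 1.00, depending on direction. The Responsiveness section counts values above 0.80 as large and above 0.50 as moderate, so the label can change.

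**The case against.** The strongest reply is that the T0/T1 difference rests on silence. A reader might infer that no tests precede scoring at T1. The article does not say so. Treatment starts or surgery is indicated at T1, so an examination there is plausible, and a journal article may leave visit detail to the full protocol. If every visit has the same sequence, most of the between-visit disturbance disappears. This stands, and the point is therefore conditional. What remains is that the T0 order is written down and nothing shown requires matching conditions later.

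A reader might also infer that every patient is injected. Taken literally, Patient routine applies the listed tests to all participants, but only two signs are needed. The injection test is one of seven for group 1 and one of six for group 2, and it is not a group 3 criterion. The share injected is unknown.

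Direction and size are unknown too. Provocation may worsen scores and lidocaine may improve them, and the two could partly offset. Nothing in the article shows that an in-clinic test moves the total WORC by 10 points; its five domains include work, social function and emotions. Test-retest is planned for the WORC only, so the most exposed instrument, the Constant Score, is affected through validity and responsiveness.

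It is tempting to add that one examiner scoring everything inflates the correlation between WORC and Constant Score, against the Background's view "making it important for measurement tools to be self-administered". The documents do not support this. Scores obtained by the examiner may simply mean forms handed out and collected. The article calls such questionnaires patient-administered, and only the Constant Score is physician-completed by design.

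Finally, taking T0 as the responsiveness baseline is not an error in itself: T0 and T1 both precede treatment, and the article expects no change between them.

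**Conclusion.** The point holds in a limited form. The article fixes a T0 order in which scores follow tests that can change pain, and it describes no matching conditions at T1 or T2. If conditions differ, the T0 scores can be biased in an unknown direction. WORC reliability, T0 validity, T0-T2 responsiveness and the hindrance check are all exposed.

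The size is not established. Under the assumed inputs the effect on the ICC runs from slight (0.943/0.935 at 5 points) to a clear miss of the target (0.888/0.833 at 15 points). In between, the answer depends on the ICC form, which the article does not state. The documents do not show that the reliability target will be missed, nor that the results are invalid. This is a real but moderate weakness in measurement order, worth correcting because the correction is cheap and the damage, if it occurs, cannot be repaired in analysis.

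**What to change.** Change Patient routine to state one measurement order for all three visits:

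- At T0 (after consent), T1 and T2, patients complete the WORC, the SF-36 and, where it is collected, the hindrance scale themselves, before any examination.
- The Constant Score is then measured before provocation tests or injection.
- The order is the same at every visit.

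This moves the measurements only; the diagnostic tests and treatment stay as they are. As an option, report responsiveness from T1 as a sensitivity analysis beside the planned T0 baseline. The T1 scores are already collected, so this needs no new data.

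The cost is a small change to visit flow, and some forms will be completed by patients who are later excluded.
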